## Abstract

**Introduction:**

Earthen floors are often damp or dusty and difficult to clean, providing an ideal environment for faecal pathogens and parasites. Observational studies have revealed associations between household flooring and health outcomes, but robust experimental evidence is scant. This study will evaluate the impact of an improved household flooring intervention on enteric infections, soil-transmitted helminth (STH) infections and tungiasis through implementation of a cluster-randomised trial in two rural settings in Kwale and Bungoma Counties, Kenya.

**Methods and analyses:**

440 clusters (households) across both sites are allocated to control or intervention group, in which a low-cost, sealed, washable, cement-based floor is installed in eligible buildings of the dwelling, alongside a floor-care guide provided during an induction meeting. Following baseline assessments in both groups, all individuals over 1 year receive albendazole and those infected with tungiasis receive benzyl benzoate. Primary outcomes are as follows: prevalence of enteric infections in children under 5 years assessed via stool surveys and PCR; prevalence of tungiasis infection in children 1–14 years based on clinical exam; and prevalence of STH infection in all household members over 1 year assessed via Kato-Katz. Secondary outcomes include the following: intensity of STH and tungiasis infections; prevalence of caregiver-reported gastrointestinal illness in children under 5; quality of life and well-being measures; and environmental contamination. A process evaluation investigates intervention acceptability, durability, practicality and cost.

**Ethics and dissemination:**

The protocol has been approved by ethics committees of The Kenya Medical Research Institute, The Kenya National Commission for Science Technology and Innovation, and The London School of Hygiene & Tropical Medicine. Following the 12-month implementation period and final assessments, control households are offered improved floors. Results will be disseminated within Kenya, to the Ministries of Health and of Lands, Public Works, Housing and Urban Development, and to subnational leadership and communities. Dissemination will also occur through publications and conference presentations.

**Trial registration number:**

NCT05914363.

STRENGTHS AND LIMITATIONS OF THIS STUDYThe study has a robust two-arm, parallel, open-label, cluster-randomised trial design powered to detect differences across study arms for three primary health outcomes.Intervention and assessment methods are informed by extensive stakeholder engagement from local to national levels as well as in-depth formative work.The study includes a detailed process evaluation for analysis of the durability, feasibility and acceptability of the improved flooring intervention.Study follow-up is limited to 12 months, and so the study will not be able to evaluate longer-term durability, sustainability and impact of the flooring intervention.

## Introduction

 Access to adequate, safe and affordable housing is highlighted in the UN Sustainable Development Goals as vital to ensuring people can fulfil their potential in a healthy environment.^1^ In sub-Saharan Africa, upwards of 840 million people are estimated to live in inadequate housing.^2^ Structurally deficient housing can expose residents to health risks, including various infectious diseases.^3^ For example, earthen household flooring that is difficult to clean, and often damp or dusty, can provide an ideal environment for the survival of faecal pathogens and parasites.^4 5^ Observational studies (predominantly cross-sectional and cohort studies) repeatedly suggest that infections with diarrhoea-causing enteric pathogens such as *Giardia*, and *Cryptosporidium* spp., and STH are higher among individuals who live in houses with earthen floors.^5^,^12^ The home is also known to be a key transmission domain for parasitic sand fleas (*Tunga penetrans*) responsible for the inflammatory skin condition tungiasis, with research linking earthen flooring to increased prevalence.^13^,^15^ Combined, these conditions are responsible for considerable morbidity and mortality in rural communities,^16^,^18^ especially when local environmental contamination is high due to inadequate sanitation or living in close proximity to animals.^1419^,^21^

Despite the potential contribution of household flooring to the burden of enteric and parasitic infections in low- and middle-income settings,^5 22 23^ there have been few experimental studies involving flooring interventions. Nevertheless, from what is available, tangible benefits to health and well-being have been demonstrated. A feasibility study in Kenya found retrofitting a low-cost, cement-based floor into homes has the potential to reduce tungiasis infection intensity.^24^ An evaluation of a programme replacing earthen with cement floors in 34 000 households in Mexico revealed reductions of 19.6%, 12.8% and 20.1% for parasite infections, diarrhoea and anaemia, respectively, in children under 5 years, alongside improvements in cognitive development.^25^ A smaller-scale evaluation in Bangladesh has reported a 72% reduction in childhood diarrhoeal episodes associated with the installation of concrete floors.^26 27^ This limited evidence suggests that while flooring interventions may be able to deliver significant improvements in community health, there is a need for high-quality experimental data, specifically powered to assess relevant health outcomes, that can accurately and reliably quantify the impacts of such interventions.

This paper describes a cluster-randomised controlled trial (RCT) evaluating the impacts of an improved (cement-based) flooring and behaviour change intervention on enteric and parasitic infections in two settings in western and coastal Kenya. Intervention design was guided by mixed methods formative research,^23^ and an associated Theory of Change.^28^

### Aims and objectives

Our primary aim is to evaluate the effectiveness of an improved (cement-based) flooring intervention in reducing the burden of enteric infections, STH and tungiasis in participating households through implementation of an RCT in two distinct settings in rural Kenya.

The primary objectives are to quantify impact on the prevalence of enteric infections, STH infections and tungiasis. Secondary objectives include assessing impact on the intensity of STH infections and tungiasis, well-being of caregivers and children, self-report gastrointestinal illness in children and the extent to which entero-pathogen and parasitic contamination of floors is reduced within the home. We will also examine the differential effects across community and household contexts (including water, sanitation and hygiene (WASH) infrastructure, animal husbandry, user adherence and study site).

Finally, we deliver a process evaluation to determine the practicality, acceptability, costs and durability of the improved flooring intervention and how environmental, installation and use factors affect these.

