**Figure 3 F3:**
[figure not shown]
Technical drawing of the improved (cement-stabilised) floor installation.

All materials are provided by the study. Installation is performed by locally recruited masons, trained by the study team, with the support of local labourers. The study team provides day-to-day supervision and quality checks using a standardised checklist for all flooring activities, and the process is overseen by the same supervisors across sites. Additionally, to ensure consistency across sites, the masons from Bungoma travel to Kwale to observe the Kwale masons at work, and the Kwale masons travel to Bungoma to partake in the training and offer advice based on lessons learnt. Household members are not expected to contribute to labour or costs of laying floors but are required to vacate their dwellings for up to 9 days while floors are laid and cured. They are also requested to assist with water provision for the floor installation and conduct the curing process and are encouraged to contribute labour during excavation where practical.

The behaviour change component, developed in consultation with the community, comprises a floor-care guide and household-level floor-care meetings. The guide is a double-sided, laminated visual aid demonstrating the ‘dos’ and ‘don’ts’ of floor maintenance including regularly sweeping and washing the floor, avoiding fire directly on the floor, and keeping animals off, where possible (online supplemental file 2). Following floor installation (and before households move back into their dwelling), trained field officers visit to address any questions and to provide advice on floor-care.

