### Trial outcomes

Primary outcomes are (1) enteric infections among children under 5; (2) tungiasis infection among children 1–14 years old; (3) and STH infection among residents of the same households who are at least 12 months of age; all of which are measured in both study arms at 0 months and 12 months (figure 1 and online supplemental file 2). A binary indicator of tungiasis infection is based on clinical examination and a binary indicator of any STH infection is assessed via Kato-Katz. For enteric infections, PCR of stool samples is used to identify prespecified enteric pathogens selected on the basis of a review of the literature:^59 41^,^43^ including *Giardia lamblia*, *Cryptosporidium* spp., *Campylobacter jejuni*, enteroaggregative *E. coli* (EAEC), *Shigella* and adenovirus, with the primary outcome based on infection with any pathogen versus none. Secondary outcomes include the following: caregiver-reported gastrointestinal illness in the last 7 days in children under 5 years; intensity of tungiasis and severity of tungiasis-associated pathology in children 1–14 years; well-being and quality of life in caregivers and children aged 8–14 years; enteric pathogen-specific prevalence among children under 5 years; and STH infection prevalence and intensity by species in individuals over 1 year.

To quantify reduction in contamination, secondary outcomes measured in both arms through environmental surveys of soil/dust samples include the following: contamination of floors with the same prespecified enteric pathogens and STH eggs/larvae (measured by PCR) and with eggs, larvae, pupae and adults of *T. penetrans* (measured using entomological screening).

Well-being in caregivers and children aged 8–14 years is measured using a range of standardised well-being and quality of life tools.

The differential effect of the intervention on the three primary outcomes (prevalence of enteric infections, STH and tungiasis) by context is examined via subgroup analysis stratified by study site and household contextual factors.

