### Process evaluation

Formative research indicated potential for heterogeneity in how household members interact with the floor and adapt behaviours such as cooking, animal husbandry and sleeping, all of which may play an important role in mitigating intervention success.^23^ A process evaluation therefore explores implementation practicality, acceptability, durability and cost.

The practicality of retrofitting a floor and the consistency of delivery across sites are assessed using internal project reporting on the following: procurement, training, flooring installation, and implementation timelines. Installation quality checklists, observations and interviews with masons, study teams and households are also used. Consistency of the delivery of the behaviour change component is measured using internal project reporting, spot-checks and interviews with intervention households. The durability of the improved floor is observed in relation to environmental, installation and use factors at three structured spot-check visits, during which performance characteristics such as crazing, cracking and blistering are assessed by engineers.

Intervention acceptability is assessed through use of space within the dwelling measured preintervention and postintervention using self-reported measures, and the practice of target behaviours measured postintervention using spot-checks and direct semistructured observations. Caregiver satisfaction is measured using semistructured in-depth interviews and structured Likert scale questionnaires administered at endline to intervention households. Costs are measured using semistructured interviews and internal project records to assemble a cost breakdown for delivering each of the intervention components.

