### Randomisation

Site-level randomisation of households to control or intervention arms is stratified by village and done through a ceremony conducted in each site upon completion of baseline assessments. The ceremony is attended by members of the study team, village-level and ward-level leadership, and representatives from participating households, who each select a sealed card, indicating group A or B. Allocation to control or intervention arms is announced after all households have drawn cards.

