### Assessments

The assessments undertaken are described below and outlined in online supplemental file 2 . Once enrolled, any household which moves house is followed up in their new location, with a note made of this, providing they are still within the study sites.

A *household questionnaire* is administered to the primary caregiver at 0 and 12 months, including questions on demographics, assets, livestock and poultry ownership and husbandry practices, WASH infrastructure and practices, and building and room uses. WASH facilities and building conditions are directly observed and GPS coordinates of the dwelling collected.

A *caregiver questionnaire* conducted with primary caregivers at 0 and 12 months includes prevalidated question modules based on the WHO Five Well-being Index (WHO-5)^48^ and WHO Quality of Life BREF (WHOQOL-BREF)^49 50^ to evaluate respondent psychological well-being, and to ask about episodes of gastrointestinal illness in the last 7 days for all children under 5 years.

A *child questionnaire* is conducted with children aged 8–14 years at 0 and 12 months comprising questions about psychological well-being and perceived quality of life drawn from the WHO-5 and the EuroQol 5-Dimension Health-related Quality of Life for Youth (EQ-5D-Y) tools.^51 52^ The modified dermatological quality of life index for tungiasis is administered to children with tungiasis.^17 53^

During the *stool survey*, all household members are invited to provide a single stool sample at 0 and 12 months for screening for enteric infections (children under 5 years) and STH infections (all residents over 1 year). Participants are provided with sample collection kits and instructed how to collect an early morning sample for collection and transport to the laboratory by the study team.

A *tungiasis assessment* is conducted with children aged 1–14 years, supported by a parent/guardian if appropriate, at 0 and 12 months by trained field workers. Diagnosis of tungiasis is made on the basis of the presence of embedded fleas and manipulated lesions in participant’s feet. The viability and number of lesions are recorded.

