### Statistical analyses

Analysis of primary and secondary human infection outcomes will be carried out on groups as randomised (intention-to-treat). Results will be presented as appropriate effect sizes (risk ratios for the primary outcomes) with a measure of precision (95% CIs), using generalised linear models with robust SE to account for correlation of outcomes within households. Prespecified analyses of impact heterogeneity will be conducted through the inclusion of interaction terms for household WASH access, ownership of livestock and socio-economic status.

Analysis of the extent to which the intervention reduces entero-pathogen and parasitic contamination of floors within the home will use generalised linear models with robust SE to estimate differences in overall pathogen prevalence in the dwelling environment at endline.

Generalised linear models with robust SE will be used to estimate differences in WHO-5 well-being index, WHOQOL-BREF (caregivers only) and EQ-5D-Y (children only) scores between study arms. Results will be triangulated with data from in-depth interviews with caregivers, which will be used to explore the pathways through which caregiver and child daily routines have changed, and if these changes have impacted well-being. Data will be coded deductively using preidentified themes and inductive coding will allow new themes to be identified while reading and interpreting transcripts. Observation data will be analysed thematically based on a case-memo approach.

Cost data will be used to estimate financial and economic costs of the intervention. Itemised costing and sensitivity analysis will enable estimation of the costs of scaled-up implementation.

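### User adherence is listed as an effect modifier although it arises after randomisation in one arm only, and study site is absent from the prespecified interaction terms

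*Protocol article*

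**What the plan says.** Three sections of the protocol article describe how the effect may vary.

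- **Aims and objectives:** the contexts are given as "including water, sanitation and hygiene (WASH) infrastructure, animal husbandry, user adherence and study site".
- **Trial outcomes:** the differential effect on the three primary outcomes "is examined via subgroup analysis stratified by study site and household contextual factors".
- **Statistical analyses:** the prespecified heterogeneity analyses proceed "through the inclusion of interaction terms for household WASH access, ownership of livestock and socio-economic status".

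Other sections fix the order of events. Randomisation is "stratified by village and done through a ceremony conducted in each site upon completion of baseline assessments". Floor-care advice comes later: "Following floor installation (and before households move back into their dwelling), trained field officers visit". Under Process evaluation, acceptability includes "the practice of target behaviours measured postintervention using spot-checks and direct semistructured observations". Assessments gives intervention households three spot-checks. Control households get two, with an adapted checklist covering debris and where and for how long daily activities take place. Ethical considerations offers controls a floor only after the final assessments.

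Study settings names the study of impact heterogeneity as one reason for choosing two sites.

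**The concern.** A valid effect modifier is fixed before allocation and defined alike in both arms, so that randomised groups can be compared within each level. Adherence to floor care meets neither condition. Households that clean and maintain a new floor well are likely to differ in hygiene, resources or time, and those traits can lower infection risk without any floor. Setting adherent intervention households against all controls would mix that selection with the effect of the floor. A trial with no effect could then appear to work where the floor is well kept, which is an attractive message for a housing policy audience.

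The second issue is site. Kwale and Bungoma differ in their reported burden of STH, diarrhoea and tungiasis, and heterogeneity is part of the case for using both. Yet the only interaction terms named do not include site. Without that test, readers are left to compare two site-specific results by eye, or by which one reaches significance, and neither shows that the effects differ.

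**Working it through.** **1. The lists side by side**

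| Section | Modifiers | Method |
|---|---|---|
| Aims and objectives | WASH, animal husbandry, user adherence, site | not stated |
| Trial outcomes | site, unnamed household factors | stratified subgroups |
| Statistical analyses | WASH access, livestock ownership, socio-economic status | interaction terms |

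The first and third share only WASH and animals. Adherence appears only in the first. Socio-economic status is named only in the third. Site is in the first two and not in the third.

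**2. Adherence and the order of events**

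The order is baseline, randomisation, installation, floor-care visit, then measurement of target behaviours. Adherence is therefore a post-randomisation variable. That controls cannot have it follows from the design, since they have neither the floor nor the floor-care component during follow-up. Their debris and activity checks record behaviour, not adherence to an improved floor.

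**3. How far selection alone could mislead (illustration, assumed inputs)**

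Assume no floor effect, 15% prevalence in both arms (the planned STH control value), half of households low-risk with relative risk r, and adherence in 80% of low-risk and 30% of other households.

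- Higher risk = 0.15 / (0.5r + 0.5); lower risk = r × higher risk.
- Adherent share = 0.5 × 0.8 + 0.5 × 0.3 = 0.55.
- r = 0.5: risks 0.10 and 0.20. Adherent: (0.40 × 0.10 + 0.15 × 0.20) / 0.55 = 0.127, RR 0.127 / 0.15 = 0.85. Non-adherent: (0.10 × 0.10 + 0.35 × 0.20) / 0.45 = 0.178, RR 1.19.
- r = 0.8: risks 0.133 and 0.167. The same steps give 0.142 and 0.159, RR 0.95 and 1.06.

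**4. The plan's own sample size**

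Inputs are from Sample size calculation; two-sided 0.05 is assumed. The stated figure is 220 households per arm.

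- STH, 15% v 10%: 686 people per arm before clustering. With design effect 1 + (5 − 1) × 0.1 = 1.4: 686 × 1.4 / 5 / 0.85 = 226 households. If loss falls on individuals (4.25 per household, design effect 1.325): 686 × 1.325 / 5 / 0.85 = 214.
- Enteric infection, 70% v 56%: 186 / 0.85 = 219.
- Tungiasis per site, 30% v 15%: 121 × 1.1 / 2 / 0.85 = 79 per arm per site, against 110 available.

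The stated 220 is reproduced. It concerns main effects; no power is given for any heterogeneity analysis.

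**5. Power for an arm-by-site interaction**

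Assume 110 households per arm per site, 15% loss, the planned control prevalence in both sites, the planned RR in one site and RR 1.0 in the other.

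Variance of log RR in a site = (1 − p1)/(n·p1) + (1 − p2)/(n·p2), summed over sites. Power ≈ Φ(|log RR| / SE − 1.96).

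- STH: n = 110 × 0.85 × 5 / 1.4 = 333.9. Variance = 0.0439 + 0.0339 = 0.0779, SE 0.279. |log 0.667| / SE = 0.405 / 0.279 = 1.45. Power about 31%.
- Enteric: n = 110 × 0.85 = 93.5. Variance = 0.0130 + 0.0092 = 0.0222, SE 0.149. 0.223 / 0.149 = 1.50. Power about 32%.
- Tungiasis: n = 93.5 × 2 / 1.1 = 170. Variance = 0.0471 + 0.0275 = 0.0745, SE 0.273. 0.693 / 0.273 = 2.54. Power about 72%.

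Without loss to follow-up the values are 35%, 37% and 79%.

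**The case against.** The best reply is that no faulty analysis is actually specified. Adherence appears once, in an objective, and is not among the prespecified interaction terms. That stands: a reader might infer that an arm-by-adherence model, or a comparison of adherent households with all controls, is planned, and the article states neither. The fault is an objective that no valid subgroup analysis can serve.

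Nor is site missing from the plan. Trial outcomes stratifies by it, and Sample size calculation evaluates tungiasis per site. Stratified estimates and interaction terms can work together, and two of the three lists are open-ended, so it would be too strong to say that all three contradict one another. What remains is narrower: the one list labelled as prespecified interactions leaves out the factor that the two-site design was meant partly to examine.

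A reader might also infer that 12-month husbandry or WASH values will define the subgroups, because the household questionnaire "is administered to the primary caregiver at 0 and 12 months, including questions on demographics, assets, livestock and poultry ownership". The article does not say so. The choice of visit is a detail that an analysis plan may hold, and livestock ownership is not the same as keeping animals off the floor.

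Finally, one could construct false RRs of 0.10 / 0.15 = 0.67 and 0.20 / 0.15 = 1.33, matching the trial's target for STH. That requires adherence to coincide perfectly with a two-fold difference in risk, which nothing in the article supports.

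**Conclusion.** The point holds in limited form. User adherence does not belong among the contexts for differential effects, because it follows randomisation and has no control-arm equivalent. Under the assumed partial sorting, selection alone moves the apparent risk ratio by about 5% to 19% in either group. Those figures depend on the assumed 80% and 30% adherence and on r between 0.8 and 0.5; they illustrate the direction and plausible size and are not estimates for this trial.

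A between-site interaction test is unstated, although heterogeneity is a declared purpose of the design. Adding it will not give a decisive answer for STH or enteric infection. The power figures also assume equal control prevalence in the two sites, which the differing background rates under Study settings make uncertain.

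The consequence is confined to secondary interpretation.

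**What to change.** 1. In Aims and objectives, delete user adherence from the list of contexts. Report it within the process evaluation, which already measures target behaviours, as a descriptive and explicitly non-randomised analysis.
2. Do not replace it with an instrumental-variable (complier-average) estimate for floor-care adherence. Households that neglect floor care still have the sealed floor, which the Intervention section expects to act by preventing direct exposure. Allocation can then affect infection by a route other than floor care, and the exclusion restriction fails.
3. In Statistical analyses, add an arm-by-site interaction. Use the same four modifiers in all three sections: site, WASH access, livestock ownership and socio-economic status. State that the household factors take their 0-month values.
4. Report each interaction estimate with its 95% CI beside the stratified estimates, and label them exploratory. State that power for site is low, and do not read a non-significant interaction as evidence of equal effects.

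The cost is wording in three sections, matching text in the analysis plan, and one added model term. No new data are needed.
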